## Measures

The primary measures for assessing the efficacy of PHMA are SBP/DBP. The secondary measures include quality of life (EQ5D-5L), hypertension-related complications, healthcare utilization and objective behaviors.

### Data collection and management

All the above measures together with data about potential confounding variables (e.g., age, sex, education, years since hypertension diagnosis) are collected at the patients’ households by trained data collectors at baseline and 12 and 24 months after baseline. SBP/DBP is measured using a mercury sphygmomanometer in accordance with standard operation specifications [31]; while the remaining data are solicited using structured questionnaires (Additional file 2) administered face-to-face by the field data collectors. Data collected at the household will be double entered using EPI DATA V3.1.

Study documentation will be kept in locked files in the offices of the project assessment supervisor and the Principal Investigator. All data will be backed-up on separate media and stored in a secure filing cabinet. Access to security passwords will be given only to the Principal Investigator and the Assessment Supervisor. Personal identifiers will not be stored in the data set and all computers will be protected by antivirus software. These data safety and confidentiality procedures are overseen by a Data Monitoring Committee.

### Data analysis

The data collected will be used to compare the differences between the control groups and the intervention group as a whole and subgroups with different intervention ingredients in the intervention arm at different time points in terms of: (a) SBP/DBP; and (b) the secondary measures including quality of life, occurrence of hypertension-related complications, healthcare utilization, and scores of objective behaviors. Estimation of statistical significance and confidence intervals will assume a type I error established in alpha = 0.05, using the IBM SPSS V22 statistics package. Despite our anticipated high follow-up rates, we expect some extent of missing data, typically participants missing an interview and are then found at the next follow-up assessment. We will use appropriate statistical techniques to estimate the missing values and then perform the analysis on the completed sample.

Initial data analysis will consist of descriptive summaries intended to examine the patterns of the various measurements and check for normality of the continuous variables. Necessary transformations will be explored and selected, if necessary, to induce approximate normality. Regarding the numerical variables between two groups, t-test of independent samples for mean comparisons will be carried out. We will also employ generalized hierarchical linear models. These models will include multiple linear regression, as well as binary, ordinal, or nominal logistic regression. In these multilevel analyses, patient-specific measurements are included in the models.

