### Study design and settings

The study adopts a cluster randomized controlled trial (RCT) design involving a total of 60 site communities with 12 in the control arm and 48 in the intervention arm. The control arm maintains existing hypertension case management; while the intervention arms, personalized hypertension management as described above. Project evaluation applies to both arms using the same data collection methods and by same field data collectors. The uneven distribution of site communities between the control and intervention arms was designed to enable detection of potential differences between the control arm and at least four main subgroups with different intervention ingredients within the intervention arm. The analysis and reporting of the trial will strictly follow the CONSORT guidelines [29, 30]. A Trial Steering Committee has been established which holds annual meetings and supervises the trial implementation. For time schedule of the trial please refer to Additional file 1.

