### Selection and randomization of communities

The RCT is implemented in Anhui, an inland province located in eastern China with a population of about 70 million living in 105 cities or counties. Selection of participating sites and patients uses a clustered randomization which proceeds in the following steps: step1 divides Anhui province into north, middle and south regions; step 2 randomly selects 4 cities/counties from each of the three regions; step 3 randomly selects five non-adjacent communities from each of the cities/counties selected; step 4 randomly selects 56 patients diagnosed with hypertension from the communities selected. The five communities selected from each city/county in steps 3 are randomly assigned to the control arm (n = 1) and intervention arm (n = 4). Hypertensive patients aged 18 years or above and capable and willing to participate in the study from the selected communities meet the inclusion criteria. All the randomization is performed by a statistical professional from outside the project team. The study will be blinded to both data collectors and analyst.

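### The named two-group test for the primary blood pressures ignores community randomisation, and no community-clustered analysis is named as the deciding one

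*Protocol article*

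**What the plan says.** Study design and settings describes a cluster randomised trial "involving a total of 60 site communities with 12 in the control arm and 48 in the intervention arm". Under Selection and randomization of communities, the five communities drawn from each of 12 cities or counties "are randomly assigned to the control arm" (one) or to the intervention arm (four). Study sample size assumes an ICC of 0.05, applies a design effect of 2.45 and arrives at 56 patients per community. Measures makes SBP/DBP primary.

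Data analysis then gives two approaches. For numerical variables compared between two groups, a "t-test of independent samples for mean comparisons will be carried out". The next sentence adds: "We will also employ generalized hierarchical linear models". These models are said to include multiple linear regression and several kinds of logistic regression. The only statement about their content is: "In these multilevel analyses, patient-specific measurements are included in the models". Significance testing "will assume a type I error established in alpha = 0.05". For missing values, the plan is to "estimate the missing values and then perform the analysis on the completed sample".

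**The concern.** The protocol sizes the trial for clustering and then names, as its most concrete between-group test, one that assumes no clustering. Patients in the same community share a practice, a neighbourhood and an allocation, so their outcomes are positively correlated. A patient-level t-test therefore has too small a standard error.

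The hierarchical models could repair this, but the text does not secure it. They are introduced as an addition, neither the community nor the city or county is named as a level or factor, and nothing says which result decides if the two approaches disagree. The sponsor could report a significant primary result from the t-test, follow the published plan in doing so, and still have a false-positive risk several times the stated 5%.

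**Working it through.** **Inputs.** From the protocol: alpha 0.05 (taken as two-sided, since the side is not stated); ICC 0.05; design effect 2.45; 20% attrition; 56 patients per community; 12 counties with 1 control and 4 intervention communities each. Assumed: the share f of the ICC that lies between counties, which the protocol does not give.

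**Step 1: the plan's own figures.** The design effect is DE = 1 + (m − 1) × ICC. The stated 2.45 is reproduced at m = 30: 1 + 29 × 0.05 = 2.45. At the planned 56 per community it is 1 + 55 × 0.05 = 3.75. With 20% lost, m = 56 × 0.8 = 44.8 and DE = 1 + 43.8 × 0.05 = 3.19. The total is reproduced: 2.45 × 228 × 5 × 1.2 = 3351.6, or 3352, and 3352 / 60 = 55.9, or 56. The 228 per arm does not follow from a difference of 5.0 and an SD of 7.8 at 90% power (these give 52). That is a separate matter, and 228 is not used below.

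**Step 2: true size of the patient-level t-test when the whole ICC lies between communities within a county.** The t-test standard error is too small by a factor 1/√DE, so

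type I error = 2 × [1 − Φ(1.96 / √DE)].

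| Patients per community | DE | 1.96/√DE | False-positive rate |
|---|---|---|---|
| 30 (implied by DE 2.45) | 2.45 | 1.25 | 21.1% |
| 44.8 (after 20% loss) | 3.19 | 1.10 | 27.3% |
| 56 (enrolled) | 3.75 | 1.01 | 31.2% |

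At DE 3.19 the t-test standard error is 1/√3.19 = 0.56 of the correct one. If the attrition allowance is read as 56 / 1.2 = 46.7 patients, the rate is 28.0%.

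**Step 3: part of the ICC between counties.** Each county contributes to both arms, so variation between counties cancels from the arm difference. The variance ratio becomes

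V = (1 − ICC) + m × ICC × (1 − f),

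and V replaces DE in the formula of step 2.

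- f = 0.5, m = 44.8: V = 0.95 + 44.8 × 0.025 = 2.07, rate 17.3%.
- f = 0.5, m = 56: V = 0.95 + 56 × 0.025 = 2.35, rate 20.1%.
- f = 0.5, m = 30: V = 0.95 + 30 × 0.025 = 1.70, rate 13.3%.
- f = 0.75: 8.9% (m = 30), 11.1% (44.8), 12.7% (56).

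With an ICC of 0.02 in place of 0.05 and f = 0, the rate is 11.9%, 15.2% and 17.6% at the same three sizes. None of these scenarios brings it back to 5%.

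**Step 4: simulation** (20,000 runs per scenario, 12 counties, 1 control and 4 intervention communities each, ICC 0.05, no true effect).

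| Patients per community | t-test, f = 0 | t-test, f = 0.5 |
|---|---|---|
| 30 | 20.8% | 13.2% |
| 45 | 27.5% | 17.5% |
| 56 | 30.8% | 20.6% |

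With one intervention community per county, as in a subgroup comparison if subgroups were formed that way, the f = 0 rates were similar: 21.0%, 27.7% and 31.4%. A within-county analysis of community means (12 differences, 11 degrees of freedom) held 4.7-5.4% in every simulated scenario, including those with ICC 0.02.

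**The case against.** The strongest reply is that the plan does not rest on the t-test. The same section plans hierarchical models and calls them multilevel; the sample size carries an ICC and a design effect; and reporting is to follow CONSORT. The paragraph that holds the t-test opens with initial, descriptive work, so the test could be meant as a first look. This stands in part: the inflated rate belongs to the t-test, and matters only if the t-test decides. It does not remove the point, because the text does not call the t-test preliminary, does not name the model as primary and does not put community in it.

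A reader might also infer more than the documents support:

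- **That the plan as a whole has a false-positive rate of 17-31%.** It does not follow, since a model with a community effect would not share that rate. The 17% end also needs half of the ICC to lie between counties, which the protocol does not state.
- **That ignoring the county block adds false positives.** Step 3 shows the opposite: the larger the county share, the lower the rate. Leaving out the block costs precision.
- **That imputation adds to the inflation.** Every figure above comes from clustering alone. The protocol says only "We will use appropriate statistical techniques to estimate the missing values and then perform the analysis on the completed sample". It does not say that imputation is single or ignores arm, and multiple imputation fits the wording. Error rates or shrinkage worked out for a particular poor method would describe a method that the protocol does not name.
- **That baseline is not adjusted for.** This is only unstated. Baseline values are collected, the sizing is on change in SBP, and regression with patient-level measurements can include them.

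**Conclusion.** The point holds in a limited form. The protocol names a patient-level t-test for between-arm comparison of numerical outcomes, primary ones included, in a trial that randomises communities, and it names no community-clustered analysis as deciding. If the t-test carries the conclusion, then at the protocol's own ICC, with no county share, a nominal 5% test has a false-positive rate of about 21-31% over 30 to 56 patients per community. If half of the ICC lies between counties, it is about 17-20% at 44.8 to 56 patients. With a smaller ICC or a larger county share it is lower, but above 5% in every scenario examined. These figures assume a two-sided test, equal community sizes and normal outcomes. This must be corrected, because a stated rule permits a wrong error rate on the primary outcome and the correction is cheap.

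**What to change.** In Data analysis, remove the independent-samples t-test for between-arm comparisons, or label it descriptive, and name one community-clustered analysis as primary for both SBP and DBP. One suitable choice is a linear mixed model with:

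- a random intercept for community, and one for patient if both follow-up visits are modelled;
- city or county as a factor, since it is the randomisation block;
- the baseline value of the outcome as covariate, which uses data already collected;
- small-sample degrees of freedom (for example Satterthwaite).

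A within-county analysis of community means is an acceptable equivalent. State which visit's contrast (12 or 24 months) decides. Use the logistic mixed counterpart for binary outcomes. If missing values are imputed, the imputation should respect arm and community.

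The cost is revised wording and slightly more programming. Confidence intervals will be wider than those of the t-test, because the t-test ones are too narrow. Design and data collection do not change.

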### Adverse events

In this study, the most likely anticipated incident is the loss of privacy, so the identification information of patients will not be placed on response forms but use an unique reference number instead.

### Dissemination

Findings from the study will be summarized for the benefit of public health policymakers, health professionals and health service managers in China and elsewhere. A final workshop will be held for the purpose of presenting the evidence generated by this study and working with local and regional stakeholders to translate this evidence into public health action.

## Discussion

PHMA introduces innovative approaches to tailor interventions to the complex and dynamic BP and related complications and contexts of individual patients. Contemporary approaches to hypertension management are mainly population-based though some studies have tried some extent of differentiated interventions, e.g., send a reminder to patients who have failed to attend an appointment [32]. PHMA uses ten categories of variables in selecting and refining intervention procedures and content for individual patients. As a result, each participant patient in PHMA applies a unique intervention package and all messages, feedbacks and other materials sent out to individual patients are different from each other. To our knowledge, PHMA is the first project that adopts so comprehensive tailoring and if proved effective, it should have important implications for future research, practice and policy-making.

PHMA adopts pragmatic strategies in securing feasibility and containing cost of interventions. It uses multiple modalities (e.g., text and sound) and venues (e.g., telephone, WeChat, Webpages, paper leaflets) in forming and disseminating intervention materials to suit various patients, especially old and illiterate ones. It strives to leverage mobile devices, self-monitoring, distant communications and computerized programs into effective, low cost, convenient and sustainable interventions. Taking the example of SMC, it may lead to a novel and cost-effective mode of interactions between patients and health professionals. Although a human professional is required to supervise the process of every SMC session, his/her workload is reduced to a large extent as compared with traditional patient-doctor communications. In a traditional communication, the doctor (or other human professional) needs to complete a whole range of activities, e.g., reviewing the patient’s status and history, forming an outline plan, and interacting with the patient; while in a SMC session, what the doctor needs to do is only to start the conversation by a brief introduction and then listen to the machine-patient interactions and add occasional queries or comments. In addition to workload reduction for the doctor, SMC may also exhibit good quality and experience for the patient, since the procedures and content are preset by an expert panel and then refined by computerized algorithms according to the actual conditions of the patient under concern.

PHMA incorporates guidance from multiple theories. As illustrated in Fig. 1, design of detailed intervention content or procedures is guided by health belief model, social cognition theory, motivational interviewing, nudging strategies and system synergy. All these theories/strategies have been used successfully in a variety of populations and settings [33–35]. Theory-informed intervention design prevents omission of important aspects and thus enhances overall efficacy [34, 36]. Each of the theories used in PHMA has its own strengths: health belief model is useful in addressing behaviors driven by rational thinking; nudging strategies apply to behaviors triggered by automatic cognitive processes [25, 28]; motivational interviewing is keen at generating and maintaining adequate momentum to leverage sustained behavior changes; system synergy informs incorporation of all intervention ingredients in a way that prevents equifinality and maximizes cost-effectiveness [27, 35, 37].

## Data Availability

Not applicable.

## Abbreviations

PHMA: Personalized hypertension management
SMC: Supervised machine communication
BP: Blood pressure
SBP: Systolic blood pressure
DBP: Diastolic blood pressure
IEC: Information, education and communication
RCT: Randomized controlled trial
